#### Secondary objectives

The key secondary objectives are to compare the superiority of app-based rehabilitation versus usual home-based rehabilitation in patients undergoing arthroplasty for knee arthritis for knee pain, knee ROM, gait speed and stability, balance, lower limb strength and lower extremity activity at 3 and 6 months. Safety outcomes include falls and knee-related hospital readmissions.

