Secondary outcomes: Other quantitative outcomes include pain, assessed using the nine-item KOOS-Pain questionnaire^15^ with a 5-point ordinal response scale, higher scores indicating higher levels of pain. Activity level will be assessed using the lower extremity activity scale,^17^ a single item self-reported question with 18 states of activity, higher numbers indicating higher level of activity. Quality of life will be assessed using the EuroQoL-5 Dimensions-5 Levels questionnaire,^18^ capturing five domains of health, namely mobility, self-care, usual activities, pain/discomfort and anxiety/depression. The overall score ranges from 0 to 1, higher score indicating better quality of life. Safety, knowledge about recovery, rehabilitation adherence, satisfaction with surgical outcome and cost incurred will be collected using study-specific questionnaires. Active and passive knee ROM^19^ of the operated knee(s) will be measured using a digital goniometer. Performance-based measurements include chair rising test to assess lower limb strength, stair climbing and 6 min walk tests to assess knee function, timed-up and go to assess gait stability,^20^ and single leg stance to assess balance.^21^ Further explanation of the measurement tools is found in table 2 and the standardised procedure to conduct the performance-based tests is illustrated in online supplemental efigure 8.

**Table 2 T2:** Trial outcomes and schedule of data collection

	Study period					
Time point	Enrolment	Baseline (0)		Visit 1 (3 months)		Visit 2 (6 months)
Screening	X		Telephonic health check-in		Telephonic health check-in	
Informed consent	X					
Health history (comorbidities)		X				
Randomisation	X					
Patient-reported outcome measures						
Knee function*		X		X		X
Knee pain†		X		X		X
Activity level‡		X		X		X
Quality of life§		X		X		X
Knee range of motion¶		X		X		X
Safety** (falls and rehospitalisation)				X		X
Knowledge about recovery††				X		
Rehabilitation adherence‡‡				X		
Cost incurred by patients§§				X		X
Satisfaction with surgical outcome¶¶						X
Performance based measures*** Function (SCT, 6MWT), Gait stability (TUG), Lower limb strength (CRT), Balance (SLS)				X		X
Process indicators††† Implementation fidelity and reach of the intervention, app usage, barriers and facilitators to implementation and end user satisfaction.						

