* Knee function assessed using the Activities of Daily Living subdomain of KOOS, a self-reported 17-item questionnaire with 5-point ordinal scale responses, with score ranging from 0 to 100, higher score indicating better knee function.

† Knee pain will be assessed using the pain subdomain of KOOS (9 items) with 5-point ordinal scale responses. Score ranging from 0 to 100, higher score indicating severity of pain.

‡ Activity level assessed using lower extremity activity scale a single item question with 18 states of activity levels, higher level indicating higher activity.

§ Quality of life assessed using EQ-5D-5L, a 5-item questionnaire capturing 5 domains-mobility, self-care, usual activities, pain/discomfort, and anxiety/depression. The score ranges from 0 to 1, higher score indicating better quality of life. Additional Visual Analogue Scale for rating current state of health (0–100).

¶ Knee range of motion-active and passive flexion and extension of operated knee(s) using digital goniometer in supine position.

** Safety—number of falls after discharge to home as reported by the family or patient and number of rehospitalisations due to index knee surgery.

†† Knowledge about recovery-14 item studyp-specific questionnaire.

‡‡ Rehabilitation adherence-22-item study-specific questionnaire.

§§ Cost incurred by the patient after surgery for physiotherapy services and medications, travel, re-hospitalisation and potential productivity loss.

¶¶ Satisfaction with surgical outcome—8-item Likert scale questionnaire.

*** Performance based measures—SCT measured as time in seconds to complete climbing up and down 12 steps of 18 cm in vertical height; 6 minute walk testT-Distance covered in 6 min at self-paced walking; TUG- Time (in secs) taken to rise from a chair of 44 cm height, walk for 3 m, turn back and be seated on the same chair. CRT-number of repetitions in 30 s to raise rising chair of 44 cm height; SLS—time in seconds an individual can stand on a single leg with eyes open.

††† Process indicators will be assessed by triangulating the findings from the screening logs, research coordinator observations, app analytics data and qualitative interviews with the end users.

CRT, chair rising test; EQ-5D-5L, EuroQol-5 Dimensions-5 Levels; KOOS, Knee Injury and Osteoarthritis Outcome Score; 6MWT, 6 Minute Walk Test; SCT, stair climbing test; SLS, single leg stance; TUG, Timed Up and Go.

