Cost analysis: Costing components will be considered from the patients’ perspective in both groups. We will assume equivalent costs for surgery, surgery-related in-hospital stays and medication in both groups and hence, costs for these components will not be collected. However, costs associated with any re-hospitalisation following discharge, either related to index surgery or other medical reasons, will be included in the analysis. Only patients who undergo unilateral or bilateral knee arthroplasty will be included in the cost analysis, and patients who will undergo knee arthroplasty of the other knee during the trial period will be excluded.

Responses to EQ-5D-5L will be converted to a single-index utility score using the Indian value set and converted into QALYs.^23^ QALY is based on the single utility score which defines the valuation of health-related quality of life from a patient’s perspective on a scale indicating 0 as ‘dead’ and 1 as ‘perfect health’. Assuming a linear trend in a patient’s utility scores from the baseline to each follow-up time point, the area under the resulting curves indicates the QALYs experienced by that patient at 6 months.^24 25^

The average of resource use, costs and EQ-5D-5L utility scores for both trial groups will be reported along with suitable method of dispersion. Comparison of cost and utility scores between two groups will be reported as mean difference and 95% CI. Bootstrapping methods will be used to address the expected skewed nature of these variables. We will report the incremental cost-effectiveness ratio representing the difference in cost for an additional QALY gained and cost per 5° knee flexion gained in the intervention group compared with usual care. Time-saving potential of the app-supported intervention as compared with the usual care will also be compared.

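### The safety outcome counts only readmissions attributed to the index knee surgery, although readmissions for any reason are to be collected for the cost analysis and could be reported by arm at little cost

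*Protocol article*

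**What the plan says.** Safety is a stated aim of the trial (Abstract; Introduction; Objectives). Its components are given in three places in the protocol article:

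- **Secondary objectives:** "Safety outcomes include falls and knee-related hospital readmissions".
- **Outcomes, Table 2, safety row:** falls and rehospitalisation, with no restriction on cause, recorded at 3 and 6 months.
- **Outcomes, Table 2 footnote on safety:** "number of falls after discharge to home as reported by the family or patient and number of rehospitalisations due to index knee surgery".

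The footnote is the fullest definition, and its second part, the "number of rehospitalisations due to index knee surgery", restricts readmissions to one cause.

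The cost analysis is wider. The Table 2 footnote on costs lists re-hospitalisation among the items, and the cost row is marked at 3 and 6 months. The cost analysis paragraph under Statistical methods says that "costs associated with any re-hospitalisation following discharge, either related to index surgery or other medical reasons, will be included in the analysis". It also limits the analysed set: "patients who will undergo knee arthroplasty of the other knee during the trial period will be excluded".

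On data capture, Outcomes says: "Safety, knowledge about recovery, rehabilitation adherence, satisfaction with surgical outcome and cost incurred will be collected using study-specific questionnaires". Under Blinding, the trial is open label, and outcomes are collected by a coordinator who is blinded to allocation and takes no part in recruitment or rehabilitation care.

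**The concern.** A readmission for a medical complication that nobody ascribes to the operation enters the cost comparison but not the safety comparison. For a trial that wants to conclude on the safety of app-supported rehabilitation, this narrows what can be said: similar counts of index-surgery readmissions would leave open whether readmissions overall were similar.

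The cause-specific count also needs someone to judge cause. The person recording the outcome is blinded, but the reason for an admission may come from the patient, the family or a treating clinician, who know the allocation. The information behind that reason may differ by arm as well. Table 1 has the app arm's clinicians monitoring progress daily in the first month and asking for images of the wound, while usual-care patients may use home services or private clinics. A knee cause could be recognised more readily in one arm. An all-cause count does not depend on that recognition.

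**Working it through.** **1. The definitions side by side**

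| Place | Readmissions covered | Used for |
|---|---|---|
| Secondary objectives | Knee-related | Safety |
| Table 2, row label | Not restricted | Safety |
| Table 2, safety footnote | Due to the index knee surgery | Safety |
| Statistical methods, cost analysis | Any reason after discharge | Cost |

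The first and third are close but not the same. A systemic complication of the operation is due to the index surgery without being a knee problem. A problem in the other knee is knee-related without being due to the index surgery.

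**2. What can be computed**

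The article gives no readmission rate, so there is no figure of the plan's own to reproduce on this point. The only input taken from it is the group size of about 150. That size does follow from its stated assumptions (effect size 0.40, two-sided alpha 0.025 per time point, 85% power, 10% loss):

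- n = 2 × (2.2414 + 1.0364)² / 0.40² = 134.3, so 135 per group
- 135 / 0.90 = 150

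It serves below only as a denominator. An added safety row does not change it.

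**3. Illustration: how much falls outside the safety outcome**

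Assumed, not from the documents: a six-month risk of 2% to 5% for index-related readmission and 2% to 5% for other readmission.

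- Expected index-related events per arm = 150 × index risk
- Expected all-cause events per arm = 150 × (index risk + other risk)
- Share outside the safety outcome = other risk / (index risk + other risk)

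| Index risk | Other risk | Index-related per arm | All-cause per arm | Share outside |
|---|---|---|---|---|
| 2% | 2% | 3.0 | 6.0 | 50% |
| 3% | 3% | 4.5 | 9.0 | 50% |
| 3% | 5% | 4.5 | 12.0 | 62.5% |
| 5% | 5% | 7.5 | 15.0 | 50% |

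At the corners of the assumed range the share runs from 2/(5 + 2) = 28.6% to 5/(2 + 5) = 71.4%.

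**4. Illustration: sensitivity to attribution**

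Assumed: all-cause risk of 8% in both arms, so 150 × 0.08 = 12 readmissions per arm and no true difference.

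| Share attributed to the surgery, one arm vs the other | Counted events | Apparent ratio |
|---|---|---|
| 50% vs 50% | 6.0 vs 6.0 | 1.0 |
| 50% vs 40% | 6.0 vs 4.8 | 0.8 |
| 50% vs 30% | 6.0 vs 3.6 | 0.6 |

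This shows how differential attribution would act. It is not evidence that it occurs.

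**The case against.** A cause-specific safety outcome is a legitimate, stated choice, and a cost analysis may use a wider set of events than a safety outcome. That stands: the two scopes do not contradict each other. The knee-related wording in the objectives can also be read as shorthand for the fuller footnote, so aligning the two is tidying.

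Several stronger readings are tempting, and the article does not support them:

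- **That attribution is unblinded.** The article does not name who judges cause, and it says that a blinded coordinator collects outcomes. Only the possibility remains that the reported cause carries knowledge of allocation.
- **That attribution decides which harms count in general.** Falls are counted without regard to cause. A fall leading to an admission not ascribed to the surgery still counts as a fall; only the admission is lost.
- **That the app replaces clinic contact.** Table 1 describes it as given on top of usual care, and both groups have clinic visits as needed.
- **That the cost analysis already holds a ready-made safety set.** It leaves out patients who have the other knee operated on during the trial. In addition, the economic paragraph under Outcomes names physiotherapy, travel and lost wages but not readmission. The case for collection rests on the Table 2 footnote and the cost analysis paragraph.

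A plain all-cause count would also bring in admissions for arthroplasty of the other knee, so these need separate handling.

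**Conclusion.** The concern holds as a minor, cheap improvement. The only readmission measure in the safety outcome is cause-specific, so medical readmissions not attributed to the surgery are left out of the comparison on a stated trial aim, although the plan intends to collect them as cost items. The readmission count, but not the fall count, depends on a judgement of cause.

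The size cannot be established from the article. The shares of roughly 29% to 71% and the apparent ratios of 0.8 and 0.6 rest wholly on assumed risks and attribution rates. With about 6 to 15 all-cause events per arm on those assumptions, either count would be mainly descriptive. The primary outcome, its analysis and the sample size are untouched. A reader might infer an error, or biased safety ascertainment; the documents show neither.

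**What to change.** - Report all-cause rehospitalisation by arm as a safety outcome for all randomised participants with follow-up data.
- Take the events from the readmission records collected at 3 and 6 months, not from the cost-analysis set. Confirm that the questionnaires record each admission and its reason.
- List admissions for arthroplasty of the other knee separately.
- Keep readmission due to the index surgery as a subset, worded the same way in Secondary objectives and the Table 2 footnote.

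**Cost:** an added table row, with the other-knee admissions shown apart, and one aligned phrase. No visit, sample size or primary analysis changes. The drawback is that all-cause counts include some events unrelated to surgery or rehabilitation; keeping the index-surgery subset beside them lets readers see both.

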### Statistical methods

#### Statistical methods for primary and secondary outcomes

Effectiveness outcomes: Baseline characteristics including mean, SD, number and percentage will be described. Mean group differences and 95% CI of KOOS-ADL score at 3 and 6 months adjusted for baseline score will be calculated using mixed effect linear regression. A p value of 0.025 will be considered as statistically significant for each of the time points. The analytical approach will be modified intention-to-treat, which includes all those who were randomised irrespective of their adherence to trial protocol if they had at least one follow-up visit after enrolment. This approach will exclude those who were lost to follow-up after enrolment.

All secondary continuous outcomes that include KOOS-Pain, ROM and performance-based measures will be compared at 3 and 6 months using linear mixed effect method adjusted for baseline KOOS-ADL, as performance-based measures will not be collected at baseline. A statistical analysis plan will be developed before the end of trial recruitment and made publicly available before final analysis. No interim analysis will be performed. The preplanned subgroups are gender and laterality of index surgery (bilateral/unilateral). Effect modification will be claimed based on interaction p<0.05. We will not perform a per-protocol analysis. Multiple imputation of missing primary outcome will be done only if more than 5% of enrolled are lost to follow-up. All analyses will be done in Stata (StataCorp) and R version 4.4.1 or higher (Postit Team, 2025).

Process evaluation: App usage (usage of diary, type of exercise prescribed and number of times therapy was modified) will be presented graphically along with suitable summary measures. The written research coordinators’ notes will be quantified using a fidelity checklist. Transcripts of qualitative interviews will be coded independently in NVivo software (Lumivero (2023) NVivo (V.14)), using an inductive-deductive approach followed by thematic analysis. The qualitative findings from the interviews, fidelity checklist, rehabilitation adherence and knowledge score, and functional outcomes will be triangulated to understand the mechanistic pathway to change, whether intervention use/non-use led to different outcomes. Further, contextual factors affecting the implementation and usage of the intervention will be summarised.

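### Stair climb and timed-up-and-go are scored only as seconds to complete, so the planned linear model has no place for a patient who attends but cannot finish

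*Protocol article*

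**What the plan says.** The footnotes to Table 2 (Outcomes) define SCT as "SCT measured as time in seconds to complete climbing up and down 12 steps of 18 cm in vertical height" and TUG as "Time (in secs) taken to rise from a chair of 44 cm height, walk for 3 m, turn back and be seated". The text gives no score, cap or category for a test that is attempted but not finished.

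The section on statistical methods for primary and secondary outcomes then fixes the analysis: "All secondary continuous outcomes that include KOOS-Pain, ROM and performance-based measures will be compared at 3 and 6 months using linear mixed effect method". The models adjust for baseline KOOS-ADL, because "performance-based measures will not be collected at baseline".

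Two further rules bear on the point. The analysis population is everyone randomised "if they had at least one follow-up visit after enrolment". On missing values the article says: "Multiple imputation of missing primary outcome will be done only if more than 5% of enrolled are lost to follow-up".

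The Outcomes section refers to supplemental eFigure 8 for the test procedure, and a statistical analysis plan is promised before recruitment ends. Neither is shown.

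**The concern.** A completion time exists only for someone who completes. For a patient who cannot manage the stairs, the result is worse than any number of seconds, and the scale cannot express it. The other three performance tests in the same footnote do not have this gap: chair rises, six-minute distance and single-leg stance time can all be zero.

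The value is missing because performance was poor. That is not missing at random, so the mixed model does not recover it. Self-reported KOOS-ADL before surgery explains it only in part. The imputation rule does not reach it either, because it covers the primary outcome and is triggered by loss to follow-up, and this patient attended.

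If the app helps, it moves some patients from unable to slow. They enter the app mean, while their usual-care counterparts enter no mean at all, and a real benefit shrinks. If treatment made patients unable, their absence would hide the harm. SCT is one of two performance tests of knee function, and gait stability, which TUG measures, is among the key secondary objectives.

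**Working it through.** **1. The plan's own figure.** The article states no figure for SCT or TUG, so the only number to reproduce is the primary sample size. Inputs from the Sample size section: effect size 0.40, power 85%, overall two-sided alpha 0.05 split over two time points (0.025 each), 10% loss.

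n per arm = 2 × (2.2414 + 1.0364)² / 0.40² = 2 × 10.744 / 0.16 = 134.3, rounded up to 135. Then 135 / 0.90 = 150, as stated. I use 135 evaluable patients per arm below.

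**2. What happens to a non-completer under the text.**

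| Step | What the article fixes | Consequence for 'attended but unable' |
|---|---|---|
| Population | Randomised with at least one follow-up visit | Patient is included |
| Measure | Seconds to complete | No value at that visit |
| Model | Linear mixed model, baseline KOOS-ADL as covariate | Patient contributes only through the other visit, if completed there |
| Imputation | Primary outcome only, triggered by loss to follow-up | Does not apply |

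**3. Size, under assumptions the article does not give.** Let latent slowness be normal with SD 1: mean 0 in usual care and −0.40 in the app arm. Patients beyond a fixed cut-off t cannot finish. If a proportion p of usual-care patients is unable, t = Φ⁻¹(1 − p), and:

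- unable in the app arm = 1 − Φ(t + 0.40)
- completer mean, usual care = −φ(t)/Φ(t)
- completer mean, app = −0.40 − φ(t + 0.40)/Φ(t + 0.40)

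For p = 10%, t = 1.2816. The usual-care completer mean is −0.1755/0.90 = −0.195. The app completer mean is −0.40 − 0.0970/0.9537 = −0.502. The difference is −0.307.

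| Usual care unable (assumed) | App unable | Completers-only difference | Share of the true 0.40 SD |
|---|---|---|---|
| 5% | 2.0% | 0.34 SD | 85% |
| 10% | 4.6% | 0.31 SD | 77% |
| 20% | 10.7% | 0.26 SD | about 65% |

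Simulation with 135 per arm gave about 0.35, 0.31 and 0.25 SD, within 0.01 of the formula. At 10%, about 14 usual-care patients (135 × 0.10) and 6 app patients (135 × 0.046) would have no time. With no true difference, the two completer means are equal and this mechanism gives no bias.

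**4. Power, with the two effects kept apart.** Simulation with assumed stair speed of mean 1.0 and SD 0.3 steps/s, an app gain of 0.12 steps/s (0.40 SD), 5% of usual care unable and a two-sided 5% test:

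- seconds, completers only: 81%
- speed, completers only: 85%
- speed, with 0 for unable: 90%

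Of the 9-point gap, about 4 points come from the change of scale and about 5 from keeping the non-completers.

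**The case against.** The strongest reply is that the article never says non-completers are set to missing or excluded. The test procedure is in eFigure 8 and the analysis plan is still to come. Coding rules commonly sit in such places, and their absence from a condensed article is no error. That stands, so a reader who infers that the protocol excludes its worst-functioning patients goes further than the text. What remains is that the article does fix a scale and a model, and any later rule for 'unable' must add something to plain seconds, such as a cap, a rank or a speed.

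Frequency is also unknown. Testing is at 3 and 6 months, patients who cannot make those hospital visits are ineligible, and TUG asks only for a rise, a short walk and a return. Non-completion of TUG is likely to be rare. In the other direction, eligibility sets no stair or walking requirement and bilateral surgery is included, so some non-completion of SCT is plausible.

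Two stronger readings should be resisted. The first is that the effect would be reversed. An example can be built: if the app only turns 5% of patients from unable into 60 s performers while all others take 30 s, the app mean is (0.90 × 30 + 0.05 × 60)/0.95 = 31.58 s against 30 s. This needs the app to help no completer at all; an ordinary shift dilutes the effect without reversing it. The second is that the whole power gap is due to lost patients; at 5% unable, nearly half of it is the change of scale.

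Finally, a patient who fails at one visit and completes at the other stays in the mixed model, which softens the loss.

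**Conclusion.** The point holds in limited form. A seconds-to-complete scale with a linear mixed model leaves 'attended but unable' without a value, and nothing else in the article supplies one. The comparison is then conditional on a post-randomisation ability. If the arms differ, it understates benefit or hides harm.

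The figures of 0.34, 0.31 and 0.26 SD for a true 0.40 SD rest on three assumptions: a normal latent scale, a uniform shift, and non-completion of 5%, 10% and 20% in usual care. They also treat one visit at a time and take no credit for information from the other visit or from baseline KOOS-ADL. The true size cannot be known from the article and may be small.

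The concern is mainly about SCT and less about TUG. The primary outcome KOOS-ADL and the sample size are unaffected. It is worth acting on because the remedy is cheap and the information may be unrecoverable if not recorded at the visit.

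**What to change.** - **Record the reason.** On the existing form, separate 'attended but unable for functional reasons' from 'did not attend'. Under Participant retention strategies, patients who miss a visit can give patient-reported outcomes by telephone, so a blank performance field could mean either.
- **Count 'unable' as the worst result** in the SCT and TUG comparisons. One option is speed, with 0 for unable: 24 steps divided by seconds for SCT, 6 m divided by seconds for TUG. For TUG this is only a rescaled time, since it includes rising, turning and sitting. A rank-based analysis with 'unable' ranked worst serves about equally well. State the choice in the analysis plan before final analysis.
- **Report the proportion unable by arm**, and give mean seconds among completers as description only.
- **If eFigure 8 or the analysis plan already has a rule**, check that it treats 'unable' as a worst result and refer to it from the outcome definition.

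The cost is one tick box and a changed secondary analysis. The downside is that the effect is no longer expressed purely in seconds, and zeros put a spike in a linear model, which is a reason to consider the rank-based form.
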